#### Secondary objectives

To examine changes in health-related outcomes during outpatient treatment with nabiximols, including mental and physical health, cognitive performance, and psychosocial functioningOther substance use (alcohol, opioids, stimulants, benzodiazepines, tobacco) are recorded by self-report number of days used in the past 28 days using the ATOP at 4-week research interview.Health outcomes and psychosocial function**.** The SF-36 [50] is administered at 4-week research interviews to assess dimensions of physical and mental health and psychosocial function. Mental health will be also be assessed using the Depression, Anxiety and Stress Scale (DASS-21) [51] at 4-weekly research interviews and the BPRS at 4-weekly medical reviews. Patient reported ratings of physical health are also assessed using the Physical Health Questionnaire-15 (PHQ-15) [52]. Pain severity and pain interference is assessed using the Brief Pain Inventory [53]. Subjective sleep ratings are assessed using the Insomnia Sleep Inventory [54]. Self-reported drug related crime (e.g. drug dealing, income generating crime) are examined using the Crime Section of the Opiate Treatment Index [55].Cognitive function is assessed by the researcher at baseline (week 0, day 1), during the maintenance phase (week 4), and at follow-up (week 24). A targeted series of computerised tests sensitive to acute THC effects are conducted, specifically an acute battery: Eriksen Flanker Task [56], Stop Signal Task [57], N-Back [58], Digit-Symbol Substitution [59], and Rapid Visual Information Processing [60] as well as a control measure (Wechsler Test of Adult Reading [61]) and a measure of memory and learning (Ray Auditory Verbal Learning Test, RAVLT [62]). At week 4 assessments, cognitive testing (acute battery) are performed 30 min prior to (trough) and 45-60 min after (peak effects) supervised dosing. Blood samples at trough and peak are taken for plasma cannabinoid levels (THC, 11-OH THC, THC-COOH, CBD, 11-OH CBD) to assist in the interpretation of findings. The acute battery uses computerised tests within the Penscreen system [63] that create random numbers for stimuli to minimise learning effects. Similarly, repeated memory assessment use parallel versions of the RAVLT. It will be of particular interest to examine whether nabiximols is associated with cognitive improvement relative to Placebo and relative to baseline. Week 24 cognitive performance assessment is examined to investigate within-subject longitudinal changes over time.Patient reported outcome and satisfaction measures: Many of the study outcomes use ‘patient reported outcome measures’ of specific domains. The Patient Global Impression of Change Scale (PGICS) [64] examines the participant’s assessment of change in their global condition at week 12 since entering treatment in the trial. Participants are also asked questions relating to their satisfaction of treatment medication and dose and their likelihood of recommending it to others.

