### Participants

#### Sample size

Based on the primary outcome measure (efficacy, safety and cost-effectiveness of nabiximols in outpatient treatment of cannabis dependence), a total sample size of 142 participants (71 per group) is required to achieve around 22% abstinence rates at 12-weeks for the placebo group (ascertained by average of previous drug administered clinical trials) and approximately 44% abstinence rates for the nabiximols group (based on clinical judgement of double the rate of abstinence than placebo) with 80% power (two-tailed) and α = 0.05.

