## Statistical analyses

Chi square and ANOVA tests will be performed to identify any baseline covariates that differ between groups. Prior to carrying out primary and secondary analysis, the percentage of missing values in the raw dataset and Little’s MCAR test will be used to determine if multiple imputation of missing values is required (except for missing urine where cannabis use will be assumed to have taken place). The multiple imputation will be done if the percentage of missing values exceeds 5%.

All analyses will use Intention-to-treat, which is defined as any person who is randomised to one of the study arms and receives at least one dose of study medications. Mixed Models for Repeated Measures (MMRM) will compare groups on changes in outcome variables (cannabis use and secondary outcomes) in the medication phase with the multiply imputed dataset, (assuming that Little’s MCAR at Random test confirms the data to be missing at random). In addition, we will perform a sensitivity analysis based on only those with complete data, and compare results to that from the MI dataset analysis.

Adverse Events will be analysed using chi-square. A Cox proportional hazards model will compare retention in treatment between study arms, controlling for potential confounds. The impact of the intervention on post-medication outcomes will compare changes in cannabis use outcomes at baseline and at follow up between groups using MMRMs.

Family-wise error corrections will control for Type 1 errors where multiple comparisons are performed within a particular analysis where post hoc contrasts are performed to further explore interesting (significant) findings.

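### Cognitive improvement on nabiximols is to be judged partly against baseline, and no between-arm comparison of week 24 cognition is stated

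*Protocol article*

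**What the plan says.** The cognitive battery is given to both arms at weeks 0, 4 and 24. At week 4 the acute tests are done twice, before and after a supervised dose (protocol article, Secondary objectives and Table 1).

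- **Question asked of cognition** (Secondary objectives): "It will be of particular interest to examine whether nabiximols is associated with cognitive improvement relative to Placebo and relative to baseline".
- **Week 24** (same section): "Week 24 cognitive performance assessment is examined to investigate within-subject longitudinal changes over time".
- **Measures against practice** (same section): the computerised tests "create random numbers for stimuli to minimise learning effects", and "repeated memory assessment use parallel versions of the RAVLT".
- **Analysis during medication** (Statistical analyses): MMRM "will compare groups on changes in outcome variables (cannabis use and secondary outcomes) in the medication phase".
- **Analysis after medication** (same section): the impact of the intervention "will compare changes in cannabis use outcomes at baseline and at follow up between groups using MMRMs".

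**The concern.** The question is about nabiximols, but the contrast with baseline does not isolate it. Its null hypothesis is that scores do not change over time, which can be false when the drug does nothing. Three features of this trial could move scores in both arms:

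- The same tasks are repeated. Randomised stimuli and parallel forms limit learning of content, and the text itself claims only to minimise it. Familiarity with the tasks can remain.
- Baseline is taken in dependent users, on tests chosen for sensitivity to acute THC effects. Reduced cannabis use could raise scores in either arm, and the sample size section itself expects about 22% abstinence on placebo. The measures against practice do nothing about this.
- Both arms receive CBT and regular clinical reviews.

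At week 24 a within-subject change mixes any nabiximols effect with all of these. The placebo arm is tested at the same visit, so the randomised comparison is collected but not assigned to an analysis. At stake is a conclusion about cognitive benefit that the randomised data may not support.

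**Working it through.** **1. Which analysis covers which visit**

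| Visit | Stated purpose (Secondary objectives) | Between-arm model (Statistical analyses) |
|---|---|---|
| Week 4 | Contrast with placebo and with baseline | Yes: MMRM on changes in secondary outcomes in the medication phase |
| Week 24 | Within-subject change over time | None stated: the post-medication MMRM names cannabis use outcomes |

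The gap is thus the whole of week 24, plus the additional baseline contrast at week 4.

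**2. The plan's own figure**

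The article says "a total sample size of 142 participants (71 per group) is required", for 22% against 44% abstinence with 80% power and two-sided α = 0.05. With a pooled variance under the null (mean proportion 0.33):

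n = [1.960·√(2·0.33·0.67) + 0.842·√(0.22·0.78 + 0.44·0.56)]² / 0.22² = (1.303 + 0.544)² / 0.0484 ≈ 70.5, rounded up to 71 per arm.

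The figure reproduces (power at 71 per arm is 80.3%). It concerns abstinence, and only the 71 per arm is used below.

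**3. What a shared shift does to a within-arm contrast**

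Inputs: n = 71 from the article. The documents give neither the shared gain d (in SD units of the score) nor the test-retest correlation r, so both are assumptions, shown as ranges. There is no drug effect.

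- SD of change = √(2(1 − r)).
- Noncentrality = d·√n / √(2(1 − r)).
- Critical value of t on 70 df, two-sided 5% = 1.994.
- Result = probability that t exceeds 1.994, that is, a significant improvement.

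Worked case, d = 0.2 and r = 0.7: SD of change = √0.6 = 0.775; noncentrality = 0.2 × 8.426 / 0.775 = 2.18; probability 0.574. The normal approximation gives 0.585.

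| Shared gain d | r = 0.6 | r = 0.7 | r = 0.8 |
|---|---|---|---|
| 0 | 0.025 | 0.025 | 0.025 |
| 0.1 SD | 0.151 | 0.188 | 0.259 |
| 0.2 SD | 0.460 | 0.574 | 0.748 |

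If only 50 in the arm are assessed (a further assumption), d = 0.2 gives 0.341 to 0.592.

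**4. The between-arm contrast**

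The expected difference in change is d − d = 0 whatever d is, so the test keeps its nominal 5% (2.5% in the favourable direction). A simulation of 20,000 trials at r = 0.7 gave two-sided rejection of 4.9% with d = 0.2 and 5.2% with d = 0.3.

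**The case against.** The strongest defence has four parts.

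- **Week 4 is covered.** The sentence on cognition names placebo first, and the medication-phase MMRM compares the arms on change in secondary outcomes. The natural reading is change from baseline compared with placebo. This stands: the randomised comparison for week 4 is already in the plan, and only the separate standing given to the baseline contrast needs wording.
- **There is no decision rule.** A reader might infer that a gain from baseline alone will be declared a nabiximols benefit, so that a false claim must follow. The documents do not support that. They specify no paired test within the nabiximols arm and nowhere say that baseline change is sufficient. The risk is of misreading, and it arises only if the change is read without the placebo arm.
- **Week 24 is not said to be within-subject only.** This is also correct. The sentence does not exclude a group-by-time model, and a fuller plan that is not shown may contain one. But the article does give that visit a stated purpose, and its two between-group models, as worded, both leave week 24 cognition out. A plan that followed this wording would carry the problem forward.
- **The percentages depend on assumed inputs.** They do, and they describe a hypothetical paired test, not the error rate of the stated MMRM. The shared gain left after randomised stimuli and parallel forms is unknown and could be small. The figures show how sensitive a within-arm contrast is; they do not forecast this trial.

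**Conclusion.** The point holds in a limited form. The article names an uncontrolled contrast as one way to link cognitive improvement to nabiximols, and states no between-arm comparison of cognition at week 24 although both arms are tested then. A gain common to both arms could make a within-arm change significant without any drug effect: about 15 to 26% of the time for 0.1 SD and 46 to 75% for 0.2 SD, against a nominal 2.5%. That range rests on 71 assessed per arm, r between 0.6 and 0.8, and a within-arm test that the plan does not itself specify. It does not show that a false claim will be made, and week 4 is largely protected by the stated MMRM. Cognition is a secondary outcome, so the severity is minor.

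**What to change.** 1. In Secondary objectives, state that nabiximols effects on cognition at week 4 (before and after dosing) and at week 24 are judged by the between-arm difference in change. The baseline score may be used as a covariate; comparing change between the arms is also valid.
2. In Statistical analyses, extend the post-medication MMRM from cannabis use outcomes to the week 24 cognitive scores.
3. Report change from baseline within each arm as descriptive only, without attributing it to nabiximols.

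The cost is a change of wording and one more model; no visits, tests or participants are added. The drawback is that the between-arm contrast is less likely to reach significance. At 71 per arm its standard error is √2 ≈ 1.41 times that of the within-arm change, and any gain shared with placebo no longer counts towards it.

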
#### Treatment ‘process’ measures

details regarding participation in trial interventions are collected on paper clinical record forms (CRF) and include details regarding doses of trial medication used (reported at weekly clinical reviews), participation in medical, counselling and clinical review sessions as well as reasons for study termination (completed protocol, treatment drop-out, medical discharge, administrative discharge, incarceration). At the completion of the ‘maintenance’ medication phase of the trial (week 12 researcher interview), participants are asked to estimate which medication group they were assigned as a means of testing the blind.

### Research procedures

#### Research interviews

The research assistant at each site conducts research interviews at weeks 0 (baseline), 4, 8, 12 and week 24. Details of the instruments and timing of administration are shown in Table 2.

#### Urinalysis and blood pathology testing

Blood and urine samples are collected in accordance with the National Statement on Ethical Conduct in Human Research (2007). All blood and urine samples are taken and stored de-identified using the patients study ID code.

Urine drug screens are collected during the medical screen and on day 1 of commencing the trial to confirm cannabis use and check for other drug use other than cannabis (prior to study medication being administered). Subsequent urine samples are collected weekly at the clinical review (and at week 24 research interview), and stored at − 20 °C until the end of the trial, with results not being available to the clinical or research staff until the completion of all data collection. The urine samples will enable cannabinoid metabolite profiles to be charted through time, as a means to identify ongoing illicit cannabis use, using creatinine corrections [65].

Blood samples are taken from all participants at baseline, week 4 (immediately before and after cognitive testing) and week 24 to determine serum cannabinoid (THC, 11-OH THC, THC-COOH, CBD, 7-OH CBD) levels. 10mls of blood are collected at each time-point and immediately centrifuged at 4 °C for 15 min at 1500 RPM and plasma pipetted into 4 × 1 ml aliquots, immediately frozen at − 20 °C. A Shimadzu 8030 triple quadrupole mass spectrometer will be used to analyse serum cannabinoids (LCMS; Shimadzu Corp, Kyoto, Japan).

## Statistical analyses

Chi square and ANOVA tests will be performed to identify any baseline covariates that differ between groups. Prior to carrying out primary and secondary analysis, the percentage of missing values in the raw dataset and Little’s MCAR test will be used to determine if multiple imputation of missing values is required (except for missing urine where cannabis use will be assumed to have taken place). The multiple imputation will be done if the percentage of missing values exceeds 5%.

All analyses will use Intention-to-treat, which is defined as any person who is randomised to one of the study arms and receives at least one dose of study medications. Mixed Models for Repeated Measures (MMRM) will compare groups on changes in outcome variables (cannabis use and secondary outcomes) in the medication phase with the multiply imputed dataset, (assuming that Little’s MCAR at Random test confirms the data to be missing at random). In addition, we will perform a sensitivity analysis based on only those with complete data, and compare results to that from the MI dataset analysis.

Adverse Events will be analysed using chi-square. A Cox proportional hazards model will compare retention in treatment between study arms, controlling for potential confounds. The impact of the intervention on post-medication outcomes will compare changes in cannabis use outcomes at baseline and at follow up between groups using MMRMs.

Family-wise error corrections will control for Type 1 errors where multiple comparisons are performed within a particular analysis where post hoc contrasts are performed to further explore interesting (significant) findings.

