### Randomisation and blinding

An independent statistician created a randomisation schedule, which was then given to the lead trial pharmacist at each site. Participants are blindly randomised in a 1:1 ratio between groups, using the variable 8-block randomisation schedule of 80 codes per site to maintain blinding. Stratification occurs at each of the four sites (aiming for a 1:1 random allocation at each site). Randomisation and group allocation happen after enrolment (informed consent) and prior to Day 1 of the study, enabling study medications to be prepared by the study pharmacist at each site. The randomisation schedule and nabiximols and placebo canisters are only identifiable to trial pharmacists at each site, who themselves have no contact with participants. All participants, clinicians and researchers involved in service delivery, data collection and analysis remain blinded to group allocation (active or placebo) until the end of the study.

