	Rey Auditory Verbal Learning Task [62]	Retention of a 15 item word list presented on 5 occasions. Number of words recalled on each presentation, following presentation of a novel list of 15 words; and then after brief and long delays recorded. Recognition of target stimuli also assessed.	Research Interview: Weeks 0, 4, 24

#### Objective 1

To examine cannabis treatment efficacy outcomes, including changes in illicit cannabis use during treatment and treatment retention.Illicit cannabis use is quantified as self-reported number of days of illicit cannabis use and average daily amount of cannabis use in grams at the 4 weekly research interviews using modified Timeline Followback [40] techniques. The primary end-point is self-reported illicit cannabis use days during the maintenance phase of treatment (weeks 1-12). Objective measures of illicit cannabis use will be determined from weekly urine collection with quantitative analysis of urinary THC, THC-COOH, CBD and other cannabinoids. 4-weekly point prevalence abstinence during maintenance phase (weeks 1-4, 5-8, 9-12), and post-treatment period (week 24) will be ascertained by combining self-report data from researcher interviews and urinalysis.Treatment retention (days in protocol treatment) are recorded from clinical records. Participants who do not attend for more than two consecutive weeks are deemed to have dropped out of treatment, and the last scheduled day of dosing is calculated as the end of treatment date.

#### Objective 2

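### Covariates are to be identified by significance tests of baseline differences between randomised arms, when they should be fixed in advance; the cost is precision and an unfixed model

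*Protocol article*

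**What the plan says.** The Statistical analyses section of the protocol article begins: "Chi square and ANOVA tests will be performed to identify any baseline covariates that differ between groups". It gives no significance threshold, no list of variables to be tested, and no statement of what follows when a variable is found to differ.

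For efficacy, "Mixed Models for Repeated Measures (MMRM) will compare groups on changes in outcome variables (cannabis use and secondary outcomes) in the medication phase". For the post-medication period, the analysis "will compare changes in cannabis use outcomes at baseline and at follow up between groups using MMRMs". Neither sentence names a covariate. The only explicit mention of adjustment concerns retention: "A Cox proportional hazards model will compare retention in treatment between study arms, controlling for potential confounds".

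Under Randomisation and blinding, allocation is 1:1 and site is the stratum: "Stratification occurs at each of the four sites (aiming for a 1:1 random allocation at each site". Under Objective 1 in Outcome and treatment process measures, "The primary end-point is self-reported illicit cannabis use days during the maintenance phase of treatment (weeks 1-12". Cannabis use over the preceding four weeks is also recorded at week 0 (Table 2), so the baseline value of this outcome is available.

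**The concern.** In a properly randomised trial, a baseline difference between arms arises by chance. A significance test of it addresses a hypothesis already known to be true. A covariate earns its place in the model by predicting outcome, and a small p-value for imbalance says nothing about that.

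The article states that the purpose of the tests is to identify covariates. If they are used that way, two things follow. The model is unknown until the data have been split by arm. And a strong predictor, such as baseline cannabis use, enters only in the few trials in which it happens to be imbalanced. Calling the Cox adjustment variables confounders, without naming them, leaves the retention model equally open. Retention matters here because Primary Objective 1 names it.

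The stakes are precision, in a trial sized at about 80% power, and a model that can be chosen after the data are seen.

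**Working it through.** **1. The plan's own sample size.** Inputs from Sample size: 22% against 44% abstinence, two-sided α = 0.05, 80% power. With pooled variance and no continuity correction, and mean proportion 0.33:

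n per arm = [1.960·√(2·0.33·0.67) + 0.842·√(0.22·0.78 + 0.44·0.56)]² / 0.22² = (1.303 + 0.544)² / 0.0484 = 70.5, so 71.

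The stated 71 per group (142 in total) is reproduced, with power 0.803. This point does not change N. The figure shows only that there is little power to spare.

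**2. Scope for chance findings.** Table 2 lists more than 20 measures taken at week 0. For m independent tests at 0.05, the chance of at least one difference is 1 − 0.95^m:
- m = 5: 23%
- m = 10: 40%
- m = 20: 64%

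Independence, the threshold and m are assumptions. Conversely, any one named variable passes the test in only about 5% of trials, however well it predicts outcome.

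**3. What the rule gives up.** The effect was set to 80% power without adjustment at 71 per arm: (1.960 + 0.842)·√(2/71) = 0.47 SD. With baseline-outcome correlation r, adjustment multiplies the outcome variance by 1 − r². Analytic power with pre-specified adjustment is then 0.836 (r = 0.3), 0.899 (r = 0.5) and 0.975 (r = 0.7).

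The selection rule was simulated with one normally distributed outcome, 142 patients, four sites and 1:1 allocation within site. There were 3,000 runs per setting under the alternative and 6,000 under the null. Test-first means adjusting for baseline only if its between-arm test gives p < 0.05, and otherwise analysing the follow-up value unadjusted.

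| r | Between-site variance | Unadjusted | Test-first | Always baseline | Baseline + site | Type I error, test-first |
|---|---|---|---|---|---|---|
| 0.3 | 0% | 0.790 | 0.793 | 0.822 | 0.821 | 4.8% |
| 0.3 | 5% | 0.805 | 0.807 | 0.836 | 0.851 | 4.2% |
| 0.5 | 0% | 0.802 | 0.812 | 0.901 | 0.902 | 4.0% |
| 0.5 | 5% | 0.788 | 0.800 | 0.892 | 0.901 | 3.8% |
| 0.7 | 0% | 0.791 | 0.812 | 0.974 | 0.974 | 3.9% |
| 0.7 | 5% | 0.807 | 0.829 | 0.971 | 0.979 | 3.0% |

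The simulation error of a power near 0.80 is √(0.8·0.2/3000) = 0.007. Test-first stays close to no adjustment throughout, and its type I error does not exceed 5%.

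**4. Site.** With 5% of variance between sites (assumed), adding site gains about 1 to 1.5 points of power, and the type I error without any adjustment is about 4.2% to 4.4%. With no site effect there is no material difference.

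**5. Change score against baseline adjustment.** The efficacy model is described in terms of change, so this comparison matters too. Let the baseline SD be k times the follow-up SD, with follow-up variance 1. Then Var(change) = 1 + k² − 2kr and Var(adjusted) = 1 − r², which differ by (k − r)². At r = 0.3 the ratio of adjusted to change-score variance is:
- k = 1: 0.91/1.40 = 0.65
- k = 0.5: 0.91/0.95 = 0.96
- k = 0.3: 0.91/0.91 = 1.00

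The gain ranges from substantial to nil, and the documents give neither k nor r.

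**The case against.** The strongest reply is that this is a condensed article. The covariate list of an MMRM is ordinarily left to the full protocol or SAP, which are not shown, and no sentence excludes baseline use or site. That stands: silence about those terms is not an error. What remains is the rule that the article does state.

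Second, the text never says that covariates found by the tests enter the MMRM, and the Cox sentence does not refer back to them. That also stands. Adjustment is the natural reading of a step meant to identify covariates, but it is an inference.

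Third, a reader might infer that baseline use is ignored. It is not, because the model concerns changes. That wording also fits a change response with baseline as covariate, or baseline as one of the repeated measures. The table in the working therefore shows what the rule does to any prognostic covariate; it does not forecast this trial's power.

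Fourth, a reader might argue that dependent users sit near the top of the use-days scale, so a change score must be inefficient. The documents give no baseline distribution, and the argument tends the other way: a compressed baseline means small k, which can shrink the penalty, as step 5 shows.

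Fifth, a reader might infer a validity problem, or standard errors materially too large because site is omitted. The simulation shows a type I error of 3.0% to 4.8% for the rule. The site effect is small, and nil if sites do not differ.

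Finally, adjusting a randomised Cox model is legitimate. The fault lies in the open list.

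**Conclusion.** The point holds as one about a poorly chosen stated method. The article identifies covariates by between-arm baseline tests and leaves the Cox adjustment set open. Used for selection, the tests respond to chance imbalance, leave the model unfixed, and forgo most of the precision that a pre-specified prognostic covariate would give: about 0.79 to 0.83 power against about 0.82 to 0.97.

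That range rests on assumed correlations of 0.3 to 0.7, an assumed 0.05 threshold, a single normal outcome and an effect set to 80% power unadjusted. The loss is also conditional on the tests actually governing the model. The documents do not support a claim of bias, of an inflated error rate, or of a definite loss against the change-score analysis. Importance is moderate to low, but the remedy is simple.

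**What to change.** Remove the baseline tests as a way of choosing covariates, and describe baseline by arm without p-values. State the model terms in advance:

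- **MMRM:** baseline cannabis use days (for secondary outcomes, the baseline value of that outcome) and site as the randomisation stratum.
- **Imputation model:** the same baseline and site terms.
- **Cox model for retention:** replace the unnamed confounders with a list fixed before unblinding, such as site and baseline use.

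If the SAP already fixes these terms, confirm that and delete the sentence on baseline tests. The cost is wording only: baseline use is collected at week 0, site is known, and N stays at 142.

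### Little's MCAR test cannot confirm missing at random, and making the imputed-data MMRM conditional on it conflicts with the 5% imputation rule

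*Protocol article*

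**What the plan says.** Three statements in the Statistical analyses section of the protocol article govern missing data.

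1. The share of missing values and Little's "MCAR test will be used to determine if multiple imputation of missing values is required". Missing urine is set apart: "except for missing urine where cannabis use will be assumed to have taken place".
2. "The multiple imputation will be done if the percentage of missing values exceeds 5"%. This sentence does not mention the test.
3. The MMRM "will compare groups on changes in outcome variables (cannabis use and secondary outcomes) in the medication phase with the multiply imputed dataset", on the stated condition that Little's "MCAR at Random test confirms the data to be missing at random".

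No analysis is named for the case in which that condition is not met. The section adds one missing-data check: "we will perform a sensitivity analysis based on only those with complete data".

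The rule reaches the primary end-point. Under Objective 1 that end-point is self-reported days of illicit cannabis use in weeks 1-12, so the missing-urine convention does not cover it.

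**The concern.** Little's test takes MCAR as its null hypothesis. It can give evidence against MCAR. It cannot separate MAR from MNAR, because that distinction concerns values nobody observed. The plan nevertheless reads the test as able to confirm MAR and attaches the main efficacy analysis to the answer.

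Two things are at stake. First, the plan could treat the MAR assumption as verified when it has not been. Second, the test result could remove the stated basis for an analysis that is valid under MAR, while another sentence still calls for imputation. The analysis of the primary end-point would then be settled only after the missing-data pattern was known.

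**Working it through.** **What the test measures.** For missingness patterns j with n_j participants, Little's statistic is

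d² = Σ_j n_j (ȳ_j − μ̂_j)ᵀ Σ̂_j⁻¹ (ȳ_j − μ̂_j), with df = Σ_j p_j − p.

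Here ȳ_j is the vector of observed means in pattern j, μ̂_j and Σ̂_j are the matching parts of the maximum-likelihood mean and covariance, p_j is the number of variables observed in pattern j, and p is the total number. Only observed means enter. A large d² says that observed values differ by pattern, which both MAR and MNAR can produce. A small d² says that no such difference was detected, and MNAR can produce that too.

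**The three statements side by side.**

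| Missing | Test | Statement 1 (share and test decide) | Statement 2 (5% rule) | Statement 3 (condition on MMRM) |
|---|---|---|---|---|
| up to 5% | not rejected | no clear call for MI | MI not triggered | met, but no imputed dataset exists |
| up to 5% | rejected | test may call for MI | MI not triggered | not met |
| over 5% | not rejected | MI | MI | met, with MAR wrongly called confirmed |
| over 5% | rejected | MI | MI | not met, no alternative named |

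The last row is the direct conflict: imputation is required, but the condition for analysing the imputed data fails.

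**Reading the condition loosely.** If missing at random is taken as a slip for MCAR, the MMRM on imputed data runs only when MCAR is not rejected. Under MCAR, imputation is least needed to avoid bias. When MCAR fails but MAR holds, imputation or a likelihood MMRM is valid and complete-case analysis generally is not, yet the condition is not met. The loose reading does not repair the rule.

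**Plan figure used.** The simulation takes N = 142 from the Sample size section. That figure reproduces. With p = 0.22 and 0.44, mean 0.33, two-sided α = 0.05 and 80% power:

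n = [1.960 √(2 × 0.33 × 0.67) + 0.842 √(0.22 × 0.78 + 0.44 × 0.56)]² / 0.22² = (1.303 + 0.544)² / 0.0484 ≈ 70.5, so 71 per arm and 142 in total.

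The point does not depend on this number.

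**Illustrative rejection rates.** The assumptions are not in the protocol: visits at weeks 0, 4, 8 and 12; normal outcomes with correlation 0.6; no treatment effect; monotone logistic dropout at a base rate of 5% or 17% per interval, giving about 14-20% or 43-48% missing at week 12; test at 0.05; 600 simulated trials per row and dropout level.

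| Mechanism (log-odds per SD; last row per unit of the residual) | Rejected, lower dropout | Rejected, higher dropout |
|---|---|---|
| MCAR | 5% | 5% |
| MAR on previous value, 0.3 | 13% | 30% |
| MAR on previous value, 0.5 | 35% | 73% |
| MAR on previous value, 1.0 | 96% | 100% |
| MNAR on current value, 0.5 | 11% | 30% |
| MNAR on current value, 1.0 | 61% | 84.5% |
| MNAR on the part of the current value not predicted by earlier visits, 1.0 | 5% | 5% |

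The simulation error is about √(0.05 × 0.95 / 600) = 0.9 percentage points at 5% and at most √(0.25 / 600) = 2.0 points.

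Under strong MAR the stated condition would be met in only 0-4% of trials. Under the last MNAR mechanism it would be met in about 95%, and under the moderate MNAR mechanism (0.5) in 100 − 30 = 70% to 100 − 11 = 89%.

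**The case against.** The strongest reply is that the third statement is a badly worded assumption in parentheses, not a decision rule, and that the 5% sentence settles when to impute. This stands in part. Read alone, that sentence brings in imputation above 5% missing whatever the test shows. A reader might infer that the plan withholds imputation when it is needed. That follows only from the first and third statements, and the second contradicts it. What the text supports is a conflict.

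A reader might also take bias in a complete-case estimate as the bias in the primary analysis. The documents do not support that, because complete case is only the sensitivity analysis and the conditioned analysis is imputation with MMRM. Nor would deleting the test remove MNAR bias, since an analysis under MAR remains exposed to it. The gain is a fixed analysis and an honest statement of its assumption.

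Three further limits stand:

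- No dropout rate is given. Study limitations warns of early termination, but Study design keeps research interviews going whether or not treatment is completed, so treatment dropout is not the same as a missing end-point.
- The test is not weak in general. Its power is high for strong MAR and near the nominal error rate for one MNAR mechanism.
- A 5% trigger fixed in advance is defensible in itself, and analysis staff stay blinded until the end of the study. Variables for an imputation model belong in an SAP.

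None of this makes the test able to confirm MAR. A likelihood MMRM on observed data would be a sound fallback, but the section does not name it.

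**Conclusion.** The point holds as an error of method and of consistency. Little's test cannot confirm MAR, so the stated condition for the imputed-data MMRM cannot be established in the way the plan describes. When more than 5% is missing and MCAR is rejected, the plan's statements disagree and the primary analysis is not determined in advance.

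The conclusion about the test rests on its null hypothesis and needs no simulation. The rejection rates (13-100% under the MAR settings, 5% to 84.5% under the MNAR settings) are illustrations that depend on assumed dropout. They show that the condition can fail where the method is valid and be met where it is not. No size of bias in the primary estimate is claimed.

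The complete-case comparison does not close the gap. It generally rests on stronger assumptions than MAR and does not probe MNAR, so agreement with the main result would not show that MAR is reasonable.

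**What to change.** In Statistical analyses, and in the SAP where it repeats the rule:

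- Remove Little's test as a decision rule. It may be reported descriptively.
- Reconcile the three statements by fixing one primary analysis under MAR, to be run whatever the test shows: either MMRM on all observed research-interview data, or multiple imputation followed by MMRM.
- State that MAR is an assumption the observed data cannot verify.
- Keep the complete-case analysis if wanted, with a note that it generally needs stronger assumptions. Name a sensitivity analysis for departures from MAR as the appropriate check.

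The cost is a change of wording plus one added sensitivity analysis. No new data are needed and the sample size stays at 142. The change should be made before the missing-data pattern is examined.
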